## Abstract

Previous work indicates the potential for community health workers and peer coaches serving as patient navigators to improve processes of care and health outcomes during care transitions, but have not been sufficiently tested to determine if such programs improve measures of patient experience in minority serving institutions. The objectives of the Patient Navigator to Reduce Readmissions (PArTNER) study was to: 1) conduct a pragmatic clinical effectiveness trial comparing a multi-faceted, stakeholder-supported Navigator intervention (in-person CHW visits in the hospital and after hospital discharge, plus telephone-based peer coaching) versus usual care on the experience of hospital-to-home care transitions in patients hospitalized with heart failure, pneumonia, chronic obstructive pulmonary disease, myocardial infarction, or sickle cell disease; 2) examine the effectiveness of the Navigator intervention in patient subgroups; and 3) understand the barriers and facilitators of successfully implementing the Navigator intervention across patient populations. The co-primary outcomes are the 30-day changes in: 1) Patient Reported Outcomes Measurement Information System (PROMIS) emotional distress-anxiety, and 2) PROMIS informational support. Secondary outcomes at 30 and 60 days include other PROMIS health measures and hospital readmissions. Innovative features of the PArTNER study include early and continuous engagement of patients, their caregivers, clinicians, health system administrators, and other stakeholders to inform the design and implementation of the Navigator intervention. In this report, we describe the design of the PArTNER study.

## Abbreviations

CHWCommunity Health WorkerCMSCenters For Medicare And Medicaid ServicesCOPDChronic Obstructive Pulmonary DiseaseDPETDischarge Patient Educational ToolDSMBData And Safety Monitoring BoardEACExternal Advisory CommitteeGEDGeneral Educational DevelopmentHIPAAHealth Insurance Portability And Accountability ActIRBInstitutional Review BoardmMissingMARMissing at RandomMCIDMinimal Clinical Important DifferenceMSIMinority Serving InstitutionNIHNational Institutes Of HealthNMARNot Missing at RandomPArTNERPatient Navigator To Reduce ReadmissionsPCORIPatient Centered Outcomes Research InstitutePPAPer-Protocol AnalysisPROMISPatient Reported Outcomes Measurement Information SystemSDStandard DeviationUI HealthUniversity of Illinois Health & Health Sciences System

## Introduction

1

Staying healthy and avoiding unnecessary healthcare utilization is valued by patients and their caregivers. Their interests converge with those of hospitals now that higher-than-expected 30-day readmissions rates place hospitals at risk for financial penalties from the Centers for Medicare and Medicaid Services (CMS) and other payers [1]. Minority-serving institutions (MSIs), defined as institutions serving in the top 10th percentile of black and other minorities, have higher risks of adverse outcomes after hospital discharge, including readmissions and death, than other hospitals [2,3]. Additionally, some states are instituting financial penalties for higher-than-expected number of readmissions for Medicaid beneficiaries, a population disproportionately served by MSIs [[4], [5], [6], [7]]. These considerations indicate that MSIs will benefit from strategies tailored to the populations they serve, including Medicare and Medicaid beneficiaries [[8], [9], [10]].

There are several well-known evidence-based strategies to decrease avoidable readmissions, including Project Re-engineered Discharge (RED), Better Outcomes by Optimizing Safe Transitions (BOOST), and Care Transitions Program [[11], [12], [13]]. These strategies employ a range of interventions, including patient education, medication reconciliation, scheduling follow-up outpatient appointments to improve care, and care coordination. Patients and caregivers at MSIs have not historically played a major role in the development of such efforts, so not surprisingly these strategies emphasize interventions delivered by clinicians to improve process measures (e.g., care coordination, reducing polypharmacy) and reducing avoidable readmissions [[14], [15], [16]]. Recent literature suggests that reducing readmissions could inadvertently increase the risk of out-of-hospital deaths [17]. Moreover, patients and caregivers have expressed concerns that programs to reduce avoidable readmissions do not adequately address some critical aspects of the patient experience during care transitions, particularly concerns about abandonment, lack of confidence in knowing what to do, and anxiety [18].

Two previous single-center clinical trials in predominantly minority low-income populations examined the role of community health workers (CHWs; lay patient advocates from the community) as in person and telephone-based patient navigators for hospitalized populations suggest the potential to increase the proportion of patients who complete follow-up appointments after hospital discharge [19,20] and to reduce hospital-readmissions within 30 days [19].

Another clinical trial found that peer-to-peer coaching delivered by telephone to caregivers of children with asthma, including Medicaid beneficiaries, can increase symptom-free days and reduce healthcare utilization (emergency department visits and hospitalizations) [21]. While these findings are encouraging, none of these clinical trials or other studies included in a systematic review commissioned by the Agency for Healthcare Research and Quality specifically examined the role of CHWs and peer coaching by telephone in improving patient experience during hospital-to-home transitions as a primary outcome [22]. These considerations suggested the need for studies testing the effectiveness of strategies to improve patient experience during hospital-to-home transitions in high-risk Medicare and Medicaid beneficiaries at MSIs.

The overall goal of the Patient Navigator to Reduce Readmissions (PArTNER) study was to conduct a randomized 2-arm parallel group, pragmatic single-center clinical trial comparing the effectiveness of CHWs and peer coaches (Navigator intervention) versus usual care to improve patient experience during hospital-to-home transitions at a MSI. The focus of the PArTNER study consisted of medical populations targeted by CMS penalties to reduce avoidable readmissions (hospitalizations for heart failure, pneumonia, chronic obstructive pulmonary disease, and myocardial infarction) and populations who disproportionately contribute to penalties among Medicaid beneficiaries at MSIs (hospitalization for sickle cell disease) [[23], [24], [25]]. The objective of this report is to describe the design of the PArTNER study and its innovative features, including the integration of existing patient advocacy organizations to deliver the Navigator intervention.

## Materials and methods

2

### Study overview and design

2.1

The PArTNER study is a two-arm randomized controlled pragmatic clinical effectiveness trial comparing the Navigator intervention to Usual care (Fig. 1). Several aspects of the study design are intended to reflect a priority to generate evidence closer to the “effectiveness” end of the continuum between efficacy (i.e., ideal conditions) and effectiveness (i.e., real world conditions) to address needs identified by end-users and a strategy that would be feasible to implement after the end of the study period (Fig. 2) [26].

**Fig. 1 fig1:**
[figure not shown]
PArTNER study design. In the PArTNER study, participants hospitalized with a physician diagnosis of heart failure, pneumonia, chronic obstructive pulmonary disease (COPD), myocardial infarction, or sickle cell disease are randomly allocated to one of two groups: Navigator intervention or Usual care. The Navigator intervention spanned over a 2-month period after hospital discharge and included: 1) community health workers (CHWs) who conducted in-person study visits in the hospital and a single home visit 1–3 days post-discharge to assess barriers to patient-centered transitions from hospital to home, and 2) peer coaches are introduced on hospital discharge and contact participants via telephone at approximately 1, 2, 3, 5, and 7 weeks post-discharge to continue supports initiated by CHWs. Following in-person baseline data collection prior to randomization, follow-up outcomes were assessed via telephone at 30 days and 60 days post-discharge.

**Fig. 2 fig2:**
[figure not shown]
Pragmatic design features of the PArTNER study according to the PRECIS-2 instrument. The study design features were based on input from patients, caregivers, clinicians, and hospital administrators during the planning stages of the PArTNER trial; goal was to develop a study consistent with a pragmatic (effectiveness) trial [26]. The “follow-up” category was graded as a 4 out of 5 as participants were contacted by phone to outcome data, rather than relying on passive approaches to data collection. Passive appraoches to data collection for assessing patient-reported measures of physical, emotional, and social health are not currently available.

### Participants

2.2

Patients hospitalized at UI Health (see Study setting, Section B.6), with a physician diagnosis of heart failure, pneumonia, COPD, myocardial infarction, or sickle cell disease are eligible for study enrollment. Trained research coordinators will use IRB-approved recruitment strategies to screen electronic health records Monday through Saturday to identify hospitalized patients with the target diagnoses. Research coordinators will contact the treating physicians to confirm the admission diagnosis documented in the electronic health record and to obtain verbal assent to approach the patient for enrollment into the study. Written informed consent will be obtained from all participants prior to enrollment. To be eligible, patients need to meet all inclusion criteria and none of the exclusion criteria described in Table 1.

**Table 1 tbl1:** PArTNER study inclusion and exclusion criteria.

Inclusion criteria	Exclusion criteria
1. Hospitalized at UI Health	1.Unable to understand and/or speak English
2. Aged 18 years or older	2. Unable/or declined to give informed consent
3. Index admission physician diagnosis of: - Heart failure, - Pneumonia, - Chronic obstructive pulmonary disease, - Myocardial infarction, or - Sickle cell disease	3. Previous participant in the PArTNER study*
	4. Planned transfer to another acute care facility
	5. Planned discharge to facility other than home (e.g., long term care facility)
	6. Receiving hospice care or planned to be discharged to hospice care
	7. Plan to leave against medical advice

Footer: UI Health – University of Illinois Hospital & Health Sciences System; * refers to patients who were re-hospitalized following completion of participation in the PArTNER study.

**Table 2 tbl2:** Community health worker (CHW)-led interventions implemented in the PArTNER study.

Component of CHW-led intervention	Description
A. Complete barrier assessment linked to socioeconomic resources	• Assessment of need for assistance with employment and income, family and social support, transportation to healthcare facilities, housing, utilities (e.g., heat, light), food, and interpersonal violence. • Barriers selected based on the Society of Hospital Medicine's Project BOOST,^16^ and interviews with stakeholders (patients, caregivers, clinicians, administrators at UI Health). • As appropriate, review barriers with the participant's clinician and social worker.
B. Offer and assist with participant-specific needs by helping patients to identify and receive assistance from resources	• Development of a tailored, patient-centered plan for solutions to each identified barrier. Resources included those available through Purple Binder (website that houses information for medical and social service resources in the Chicago area) and those used by the hospital's social work department. • Review of solutions with the participant during subsequent visits and/or through email and text messages. • Reassessment of barriers and identification of new ones during each CHW in-hospital encounter. • Caregivers included in the discussions if requested by participant.
C. Completion of a “Discharge Patient Education Tool”	• Completion of personalized discharge patient educational tool (DPET) based on discharge instructions in the electronic health records. • Core content areas reviewed with participant using teach-back: - Post-discharge follow up visits and tests, - Recommendations regarding lifestyle changes, and - Use of medications after discharge. • CHW scheduled post-discharge follow-up appointments as needed. • Review of previously-identified barriers and potential solutions, including post-discharge resources and services. • Scheduling of home visit of CHW within 3 business days of hospital discharge. • Referral to the participant's clinicians for medical advice. - The CHWs were specifically instructed to not provide medical advice.
D. Re-review the DPET with the participant	• During home visit, review of DPET with the participant, including: - Reminder of upcoming tests and appointments - Confirmation of availability of transportation to tests and appointments - Review understanding and adherence to lifestyle changes - Confirmation of availability of medications - Confirmation of understanding and adherence to medications • If the participant had difficulty adhering to the DPET, peer coached identified new barriers and worked with participant to find a solution. • Participants encouraged to contact the hospital's social worker or clinician's office, if needed.
E. Re-review solutions to barriers with patient	• Review solutions implemented for previously identified barriers. • If needed, identification of new barriers and potential solutions
F. Peer coaching	• Introduction of peer-coaching intervention prior to hospital discharge. • Reminder about upcoming phone-based peer coaching calls during the home visit. • Peer coaches had access to barriers and solutions identified by CHW through study data system.

**Table 3 tbl3:** Peer coach intervention components.

Peer Coach Component	Description
A. Greeting and Reminder	IRB-approved script used to confirm the participant's identity and remind them of their participation in the study.
B. Review of the participant's DPET.	• Review of DPET with the participant, including: - Reminder of upcoming tests and appointments - Confirmation of availability of transportation to tests and appointments - Review understanding and adherence to lifestyle changes - Confirmation of availability of medications - Confirmation of understanding and adherence to medications • If the participant had difficulty adhering to the DPET, peer coached identified new barriers and worked with participant to find a solution.
C. Review previous barriers and solutions.	• Review of previously-identified barriers and potential solutions • Identification of new barriers and potential solutions (similar procedure as CHW)
D. Schedule next peer coaching intervention call.	• Schedule next (of five) peer coaching intervention call: - Participants offered flexibility in scheduling according to their availability - Last call occurred by 60 days post-discharge.

### Randomization

2.3

Following baseline data collection, we will employ block-stratified randomization with permuted blocks to promote balance in the number of participants in each of the two PArTNER study groups (Navigator intervention and Usual care) in three key baseline participant characteristics: 1) enrollment condition (heart failure, pneumonia, COPD, myocardial infarction, or sickle cell disease); 2) baseline anxiety (Patient Reported Outcomes Measurement Information System [PROMIS] emotional distress-anxiety v1.0, SF4a,T-score ≥50, yes/no); and 3) baseline informational support (PROMIS informational support, v2.0, SF4a, T-score ≥50, yes/no) [27]. The random allocation sequence will be generated by a computerized random number generator. Strata will include baseline values of anxiety (PROMIS emotional distress-anxiety) and informational support (PROMIS informational support), since changes from baseline values for emotional distress-anxiety and informational support at 30 days were the co-primary outcomes. Research staff will be masked to treatment allocation sequence prior to informed consent and baseline data collection as our data system required this information to generate a treatment allocation. Research staff collecting post-randomization outcomes will also be masked to treatment allocation as they do not have access to treatment-related information.

### Power and sample size

2.4

Assuming 20% attrition and a Bonferroni correction for two co-primary outcomes (2-sided alpha 0.025), we estimate that 1,130 participants (565 participants in each treatment group) are needed for 95% or greater power to detect a 2.5 unit difference (25% of a standard deviation, or T-score of 2.5) for each of the co-primary outcomes in the overall population. The minimum detectable difference in T-score of 2.5 falls well within the T-score minimal clinical important difference (MCID) of 2–5. The 95% power for the primary outcomes was selected to allow the calculated sample size to also provide 80% power to detect a 7.5% absolute reduction in 30-day risk of death or re-hospitalization (from 30% to 22.5%) and 90% power to detect a 10% reduction.

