#### Primary outcomes

2.10.1

Patient and caregiver engagement activities indicated the need for two co-primary outcomes for the clinical trial:1.Change in participant anxiety from baseline (enrollment to 30 days post-discharge).2.Change in participant informational support (enrollment to 30 days post-discharge).

Informational support refers to the ability to obtain advice, guidance, suggestions, or useful information.

We will use the National Institutes of Health (NIH) PROMIS measures for our co-primary outcomes, since the development and validation of PROMIS scales have been extensively documented [27]. The PROMIS emotional distress-anxiety short form (version 1.0 SF4a, 4 items) will be used to assess participant anxiety in the previous 7 days. The PROMIS informational support short form (version 2.0 SF4a, 4 items) will be used to assess informational support among study participants in the previous 7 days. For PROMIS measures, raw scores for each measure will be re-scaled into a standardized T-score with a mean of 50 and standard deviation of 10 for the US general population [27,32,33]. Higher PROMIS T-scores indicate more of the concept being measured (e.g., higher anxiety T-scores indicate more anxiety). Studies suggest that a 2- to 5-unit or greater difference in T-scores is likely to be the MCID, though the MCID following hospital discharge in the target population has not been established.

Using PROMIS measures confers several distinct advantages: 1) *Comparability*—measures have been standardized to be patient-centered, rather than disease-specific, permitting comparisons of patient outcomes between the Navigator and Usual care groups despite enrolling patients with multiple conditions; 2) *Reliability* and *Validity*—metrics for each domain have been rigorously reviewed and tested; 3) *Flexibility*—PROMIS measures can be administered in a variety of ways (in person, telephone, or via computer adaptive testing); for PArTNER, the baseline visit occurred while the patient was in the hospital, so administration was in person. Follow-up visits were performed by telephone to minimize participant burden (a key principle in effectiveness trials); and 4) *Inclusiveness*—PROMIS encompasses all people, regardless of literacy, language, physical function, or life course.

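### On its own inputs, section 2.4 gives about 93.5% power for each co-primary outcome, slightly below the stated floor of 95%

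*Protocol article*

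**What the plan says.** All inputs to the power statement are in the protocol article, section 2.4 (Power and sample size). It begins "Assuming 20% attrition" and applies a "Bonferroni correction for two co-primary outcomes (2-sided alpha 0.025"). It then states that "1,130 participants (565 participants in each treatment group) are needed for 95% or greater power to detect a 2.5 unit difference" on each co-primary outcome. The difference is described as a "2.5 unit difference (25% of a standard deviation, or T-score of 2.5"), which fixes the SD at 10.

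Section 2.10.1 (Primary outcomes) defines the first co-primary outcome as "Change in participant anxiety from baseline (enrollment to 30 days post-discharge"); the second is the corresponding change in informational support. The same section describes the PROMIS scaling as a "standardized T-score with a mean of 50 and standard deviation of 10 for the US general population".

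Section 2.11 (Analytical and statistical approaches) makes the primary analysis a linear regression of the change, adjusted for listed baseline characteristics. Participants without the co-primary outcome are left out. The list does not include the baseline PROMIS score.

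**The concern.** The power is worded as a floor of 95%, and 1,130 is given as the number required to reach it. A reader can check this directly, because alpha, attrition, difference and SD are all stated. Under a complete-case analysis, attrition reduces the number analysed, and the reduced number does not reach the floor.

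What is at stake is how a null result on either co-primary outcome would be read. The power statement tells readers which differences the trial could be expected to detect, so it should agree with its own inputs.

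**Working it through.** **Inputs (section 2.4).** 565 per arm; attrition 20%; two-sided alpha 0.025; difference 2.5; SD 10, from 2.5 being 25% of an SD. Completers per arm: 565 × 0.8 = 452.

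**Power as stated.** For an unadjusted comparison of two means:

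- Noncentrality = (2.5/10) × √(452/2) = 3.758.
- Critical value z(0.9875) = 2.241.
- Power = Φ(3.758 − 2.241) = Φ(1.517) = 0.935. The noncentral t distribution also gives 0.935.

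The stated figure is 95% or more; the result is 93.5%.

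**Size needed for 95%.**

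- n = 2 × (2.241 + 1.645)² / 0.25² = 483.3, so 484 completers per arm.
- 484 / 0.8 = 605 randomized per arm, or 1,210 in total. This is 80 (7%) more than 1,130.

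**Do other readings of the inputs give 95%?**

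| Reading | Analysed per arm | Power |
|---|---|---|
| As stated | 452 | 93.5% |
| Attrition allowed for by multiplying by 1.2 (565/1.2) | 471 | 94.4% |
| No attrition | 565 | 97.5% |
| Alpha 0.05 instead of 0.025 | 452 | 96.4% |

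Only the last two reach the floor, and each drops a stated input.

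**What 1,130 does deliver at 95% power.**

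- Detectable difference with 452 per arm: (2.241 + 1.645) × 10 × √(2/452) = 2.585, about 2.6.
- Attrition that leaves 484 of 565: 1 − 484/565 = 14.3%, so about 14% or less.
- Largest SD that keeps 95% power for 2.5 units: 2.5 / (3.886 × √(2/452)) = 9.67.

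**The SD of a change score.** If each time point has SD 10 and the baseline to 30-day correlation is ρ, the change has SD 10 × √(2(1 − ρ)). The article gives no ρ; the values here are assumptions.

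| ρ | SD of change | Power, 452 per arm |
|---|---|---|
| 0.3 | 11.8 | 82.5% |
| 0.4 | 11.0 | 88.3% |
| 0.5 | 10.0 | 93.5% |
| 0.6 | 8.9 | 97.5% |
| 0.7 | 7.7 | 99.5% |

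The 95% line is crossed where 2(1 − ρ) = 0.967², that is at ρ of about 0.53.

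**With the baseline score as a covariate.** On the same assumption of SD 10 at both times, the residual SD is 10 × √(1 − ρ²). It is 9.67 or less when ρ ≥ √(1 − 0.967²) = 0.255, so about 0.26 or more. At ρ = 0.3 the residual SD is 9.54 and power is 95.5%; at ρ = 0.5 they are 8.66 and 98.2%.

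**The case against.** **The gap is small.** It is 1.5 points, the detectable difference of 2.585 stays within the MCID range that section 2.4 cites, and no test or decision rule changes. This stands, and it limits the point to a correction of a stated figure. It does not make the figure right, because the text sets a floor and does not say about 95%.

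**The primary model is adjusted.** The covariates in section 2.11 could bring the residual SD down to 9.67 by explaining about 6.5% of the variance (1 − 0.967² = 0.065). That is possible, and for this reason 93.5% is given here as the figure for an unadjusted comparison. But section 2.4 claims no such reduction and states no R², so the adjustment cannot be used to support its figure.

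**A stronger reading.** A reader might infer that power is seriously overstated because 10 is the general-population SD of a single T-score while the endpoint is a change. The document does not support this. Section 2.4 does not say which SD is meant, and an SD of change of 10 fits its wording equally well. The direction depends on a correlation that is not given: power falls below 93.5% for correlations under 0.5 and exceeds 95% from about 0.53. These figures also assume SD 10 at both time points in this hospitalized population, which the article does not state. A condensed article may leave the justification of the SD to the full protocol or analysis plan.

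**Conclusion.** The stated power is wrong as written, by a small amount. With 452 completers per arm, SD 10, a difference of 2.5 and a two-sided alpha of 0.025, power for each co-primary outcome is about 93.5% in an unadjusted comparison, against a stated 95% or greater. This rests on the article's own inputs and its complete-case rule, and on reading the SD of 10 as the SD of the 30-day change.

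A reader might go on to infer that the trial is underpowered or must enrol 1,210. Neither follows. At SD 10 the trial remains well powered, and the shortfall corresponds to a detectable difference of about 2.6 instead of 2.5.

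**What to change.** Restate section 2.4 without adding patients: 1,130 participants with 20% attrition give about 93% power for a difference of 2.5 units, and 95% for about 2.6, at a two-sided alpha of 0.025. Say that the SD of 10 is taken as the SD of the 30-day change. The cost is one sentence and a slightly less favourable figure.

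Alternatively, add the continuous baseline PROMIS score for each outcome to the covariates in section 2.11. The score is already collected before randomization, and that section already provides for the list to be finalized while masked to allocation. Power is then at least 95% if the baseline to 30-day correlation is about 0.26 or more and both time points have SD 10. If this route is taken, section 2.4 should state the correlation assumed.

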All analyses will be conducted using a modified intention-to-treat principle, in which we ignored the individual with the missing data for the co-primary outcomes (complete-case analyses). To assess the sensitivity of results to the complete-case analyses, we will conduct multiple imputations under a missing at random (MAR) assumption [34]. We will also conduct multiple imputations under a missing not at random (MNAR) assumption under a joint selection model of outcome and missingness and employ Bayesian analyses for each of the two co-primary outcomes. Our multi-tiered approach to missing data will be used to determine if the Navigator intervention effects are qualitatively maintained across various approaches to handling missing data. We will also conduct per-protocol analyses (PPAs) for the primary outcome. In the PPAs, the Navigator intervention will be considered per-protocol if the participant received both hospital and home-based components of the CHW-led interventions and at least one peer-coaching call. We will employ a 2-sided Bonferroni-corrected alpha of 0.025 (and 97.5% confidence intervals, CIs) for the two co-primary outcomes in the multivariable analyses, and a 2-sided alpha of 0.05 (and 95% CIs) for all other hypothesis tests.

We will also conduct exploratory analyses to assess the potential for heterogeneity of treatment effects for the primary outcome by examining the consistency of the adjusted differences in pre-specified subgroups (across levels of each baseline characteristic) in a series of linear regression models with covariates that included the treatment-group indicator, the treatment-by-subgroup interaction terms, and all other covariates in the multivariable models. We will also collect a limited number of baseline characteristics in keeping with information that is routinely collected on hospitalizations and that have been associated with hospital readmissions at MSIs [35]. The p-values for consistency of adjusted differences in linear or logistic regression models across subgroups will be determined by Wald chi-squared tests. The PArTNER study was not specifically powered to assess heterogeneity of treatment effects, so all such analyses should be considered exploratory. Due to multiple hypothesis tests, we will employ Bonferroni corrections to reduce the risk of a type 1 error.

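### The 80% power stated for 30-day death or re-hospitalization needs about 540 analysed per arm; the complete-case rule, applied to all analyses, would leave 452 per arm and about 73% power

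*Protocol article*

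**What the plan says.** Section 2.4 (Power and sample size) sets the trial at "1,130 participants (565 participants in each treatment group"). The calculation opens with "Assuming 20% attrition and a Bonferroni correction for two co-primary outcomes (2-sided alpha 0.025") and targets the two PROMIS co-primary outcomes. It adds that the 95% power for those outcomes was chosen so that the same sample size would "also provide 80% power to detect a 7.5% absolute reduction in 30-day risk of death or re-hospitalization (from 30% to 22.5" percent), "and 90% power to detect a 10% reduction". No analysed n or alpha is attached to these last two figures.

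Section 2.11 (Analytical and statistical approaches) supplies both, at least by its wording. It sets "a 2-sided alpha of 0.05 (and 95% CIs) for all other hypothesis tests", which covers this secondary endpoint. It also places all analyses on a modified intention-to-treat set "in which we ignored the individual with the missing data for the co-primary outcomes", and makes no exception for outcomes that do not come from the telephone interview.

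Section 2.10.2 (Secondary outcomes) says how this endpoint is ascertained: re-hospitalization by review of electronic health records, death by caregiver report or the same records. Section 2.8 says the patient-reported outcomes are collected by telephone.

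**The concern.** The three sections do not fit together for death or re-hospitalization. Section 2.4 quotes a power that is reached with nearly everyone analysed. Section 2.11, as worded, analyses only participants with co-primary PROMIS data, and section 2.4 expects to lose 20% of participants. Section 2.10.2 describes an endpoint whose collection does not depend on the PROMIS interview.

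Two things are at stake. First, section 2.4 gives this 80% as a reason for choosing the primary power, so it is part of the justification for 1,130 participants. If the analysis follows section 2.11 literally, a null result on this endpoint would be judged against a power the analysis did not have. Second, a participant who dies before the 30-day interview has no 30-day PROMIS score. Dropping that participant removes an event from an endpoint that counts deaths.

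**Working it through.** **Inputs**
- Randomised per arm: 565 (section 2.4).
- Attrition: 20% (section 2.4), giving 0.80 × 565 = 452 per arm with PROMIS data.
- Event risks: 30% vs 22.5% (section 2.4). The 10% reduction is taken as absolute, 30% vs 20%; this is an assumption, made to match the absolute 7.5% beside it.
- Alpha: two-sided 0.05 (section 2.11, all tests other than the co-primaries), so z = 1.96.

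**Formula** (two proportions, equal arms of size n, pooled variance under the null, p̄ the mean of p1 and p2):

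power = Φ{ [ |p1 − p2| − z·√(2p̄(1 − p̄)/n) ] / √( [p1(1 − p1) + p2(1 − p2)]/n ) }

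For 30% vs 22.5%: p̄ = 0.2625, 2p̄(1 − p̄) = 0.3872, and p1(1 − p1) + p2(1 − p2) = 0.2100 + 0.1744 = 0.3844.

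**Step 1. Reproduce the stated 80%, n = 565**
- Null SE = √(0.3872/565) = 0.02618; times 1.96 = 0.0513.
- Alternative SE = √(0.3844/565) = 0.02608.
- (0.0750 − 0.0513)/0.02608 = 0.908, so power = 81.8%.
- With a continuity correction it is 80.0%. The stated figure is therefore reproduced with everyone analysed.

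**Step 2. Same effect, n = 452**
- Null SE = √(0.3872/452) = 0.02927; times 1.96 = 0.0574.
- Alternative SE = √(0.3844/452) = 0.02916.
- (0.0750 − 0.0574)/0.02916 = 0.605, so power = 72.7%.
- Other formulas give 70.2% (continuity-corrected), 72.9% (arcsine) and 73.0% (unpooled), so the choice of method does not restore 80%.

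**Step 3. How much loss the 80% tolerates**
- n = [1.96·√0.3872 + 0.8416·√0.3844]² / 0.075² = 3.032/0.005625 = 539.1, i.e. 540 per arm.
- 1 − 540/565 = 4.4%. With the continuity correction the requirement is 566 per arm, which leaves no room for loss.

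**Step 4. The 10-point effect, 30% vs 20%** (p̄ = 0.25; the two variance terms are 0.375 and 0.370)
- n = 565: (0.1000 − 0.0505)/0.02559 = 1.935, power 97.3%.
- n = 452: (0.1000 − 0.0565)/0.02861 = 1.522, power 93.6%.
- 90% power needs 392 per arm, so the stated 90% is met in both analysis sets.

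| Analysed per arm | 30% vs 22.5% | 30% vs 20% |
|---|---|---|
| 565 (all randomised) | 81.8% | 97.3% |
| 540 | 80.1% | 96.8% |
| 452 (20% excluded) | 72.7% | 93.6% |
| Stated in section 2.4 | 80% | 90% |

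**The case against.** The best reply is that the 80% is correct and was meant for all 1,130 participants. The 20% attrition stands in the sentence that sizes the PROMIS outcomes, which are collected by telephone. Re-hospitalization comes from health records, so a participant who cannot be reached by phone still has data for this endpoint. The complete-case wording is framed around missing co-primary data, and a rule that drops the dead from an analysis of death is unlikely to have been intended.

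Much of this stands. The power figure is not a miscalculation, and 565 per arm is a defensible basis for it. But section 2.11 says all analyses and exempts nothing, so the reply holds only if that sentence does not mean what it says for this endpoint. That calls for an amendment, not a guess at intent.

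Three stronger readings are tempting, and the documents do not support them:
- That the 80% holds only with no attrition. By the pooled formula it tolerates about 4%.
- That 80% and 90% contradict each other because one sample size cannot give exactly both. Read as minimums, 565 per arm satisfies both, and the 90% merely understates.
- That this endpoint will certainly lose 20%. The loss follows from the literal complete-case rule, not from how the endpoint is collected.

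A reader might also carry the 0.025 over from the co-primary outcomes, which would give 73.4% at 565 per arm. Section 2.11 sets 0.05 for this test.

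**Conclusion.** The stated 80% is sound for an analysis of all randomised participants and not for the analysis set that section 2.11 prescribes. On that set, with the plan's own attrition, power for 30% vs 22.5% is about 73%: a type II error of 27% where 20% is claimed. The 10-point claim is safe either way.

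The 73% is conditional. It assumes that section 2.11 is applied as written, that exclusions are 20% in each arm, that the 30% and 22.5% risks hold among those who remain, and that the comparison is unadjusted. The documents give no expected number of deaths, so the effect of dropping early deaths on the event rates cannot be sized here. The point concerns one secondary endpoint, though one that section 2.4 uses to justify the sample size. It says nothing against the co-primary analyses.

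**What to change.** 1. In section 2.11, limit the complete-case rule to the PROMIS outcomes.
2. In the same place, state that death and re-hospitalization are analysed in all randomised participants by assigned group, whether or not the 30-day interview was completed.
3. In section 2.4, state that the secondary figures refer to 565 per arm at two-sided 0.05: about 82% for 30% vs 22.5% and about 97% for 30% vs 20%. Say that the 10% reduction is absolute.
4. If the complete-case set is kept for this endpoint, restate the figures as about 73% and 94%, and say how participants who die before the 30-day assessment are handled.

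The cost is a sentence or two in each section, with no added recruitment or data collection, since section 2.8 already plans record review. Keeping both the complete-case set and 80% power would instead need 540/0.80 = 675 per arm, or 1,350 randomised. Two limits remain under the preferred fix: section 2.10.2 says care outside the health system is not captured, and a death known only to a caregiver may be missed when nobody can be reached. Both are limits of ascertainment to be reported, not reasons to exclude participants.
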